## Abstract

**Background:**

Real-world data for patients with chronic kidney disease (CKD), specifically pertaining to clinical management, metabolic control, treatment patterns, quality of life (QoL) and dietary patterns, are limited. Understanding these gaps using real-world, routine care data will improve our understanding of the challenges and consequences faced by patients with CKD, and will facilitate the long-term goal of improving their management and prognosis.

**Methods:**

DISCOVER CKD follows an enriched hybrid study design, with both retrospective and prospective patient cohorts, integrating primary and secondary data from patients with CKD from China, Italy, Japan, Sweden, the UK and the USA. Data will be prospectively captured over a 3-year period from >1000 patients with CKD who will be followed up for at least 1 year via electronic case report form entry during routine clinical visits and also via a mobile/tablet-based application, enabling the capture of patient-reported outcomes (PROs). In-depth interviews will be conducted in a subset of ∼100 patients. Separately, secondary data will be retrospectively captured from >2 000 000 patients with CKD, extracted from existing datasets and registries.

**Results:**

The DISCOVER CKD program captures and will report on patient demographics, biomarker and laboratory measurements, medical histories, clinical outcomes, healthcare resource utilization, medications, dietary patterns, physical activity and PROs (including QoL and qualitative interviews).

**Conclusions:**

The DISCOVER CKD program will provide contemporary real-world insight to inform clinical practice and improve our understanding of the epidemiology and clinical and economic burden of CKD, as well as determinants of clinical outcomes and PROs from a range of geographical regions in a real-world CKD setting.

## INTRODUCTION

Chronic kidney disease (CKD) is a major global public health problem resulting in a substantial financial and resource burden on healthcare systems worldwide according to the Global Burden of Disease (GBD) CKD Collaboration [1]. Based on a serum creatinine–based estimated glomerular filtration rate (eGFR) and urinary albumin:creatinine ratio, the Kidney Disease: Improving Global Outcomes group developed a classification system that is now widely used in clinical practice to diagnose and stratify risk in patients with CKD [2]. Using this classification, the global prevalence of identified CKD from all causes and all stages is ∼9%, equivalent to ∼700 million individuals. Since 1990, the prevalence of CKD has increased by 29% worldwide [3]. According to the most recent GBD Study, CKD is the 12th leading cause of death worldwide; in addition, CKD resulted in 36 million disability-adjusted life years, with diabetic kidney disease accounting for almost one-third of this burden [1].

Patients with CKD commonly experience an accelerated and progressive loss of kidney function and are at risk of progression to kidney failure [4]; kidney replacement therapies are lifesaving but costly. CKD is also associated with comorbidities including diabetes, hypertension, hypercholesterolemia and heart failure, as well as an increased risk of myocardial infarction and death [2].

Progressive CKD also negatively affects quality of life (QoL) and multiplies the risk of morbidity and mortality, particularly from cardiovascular causes [5]. In general, the management of patients with CKD involves preventing or slowing the progression of kidney disease, managing the complications of progressive kidney failure and preventing and managing the disease and complications in other organ systems, such as the cardiovascular and central nervous system [6–9]. In many cases, specific treatment of the underlying disease (i.e. glomerular and tubulointerstitial diseases as well as systemic diseases that affect the kidney) offers an opportunity to halt or mitigate CKD progression. For many others, measures to slow the rate of progression in patients with CKD are centered on blood pressure goals and, in patients with proteinuric disease, on reducing proteinuria with the use of angiotensin-converting enzyme inhibitors or angiotensin receptor blockers [8]. Dietary (i.e. protein restriction and a reduction in sodium intake) and lifestyle (physical activity and smoking cessation) interventions/changes may also reduce the risk of CKD progression [10]. Unfortunately, recent reports have identified that general recommendations to reduce the progression of CKD are suboptimally implemented in real-world clinical practice [11]. Revised recommended targets for blood pressure and diabetes management are now available across CKD stages [8, 9], but to what extent these recommendations will be implemented remains to be determined.

Management of CKD should also encompass the wide range of disorders and complications that develop because of the loss of kidney function. These disorders include, but are not limited to, volume overload; hyperkalemia; metabolic acidosis; difficulties in glycemic control and dyslipidemia; CKD mineral and bone disorders; cardiovascular and coronary heart diseases; signs and symptoms related to hormonal or systemic dysfunction such as anorexia, nausea, vomiting, fatigue, anemia and protein-energy wasting; as well as neuropsychiatric conditions such as depression, anxiety disorders and cognitive impairment [12–22]. The management of these complications is important in patients with CKD to reduce the risk of morbidity and mortality, reduce symptomatic burden and improve QoL [23]. Similar to what has been observed in the treatment of CKD progression, best practices recommended by guidelines and new therapies to manage these CKD complications are vastly underutilized in real-world clinical scenarios [19, 24].

Finally, there is growing interest in patient-centered care, defined as ‘care that is respectful of and responsive to individual patient preferences, needs and values’ [25]. In this horizon of important shifts in the CKD management paradigm, the inclusion of digital health solutions to capture patient-reported outcomes (PROs), including innovative ways of capturing the patients’ voice and disease awareness, is essential [26, 27].

We hypothesize that there is significant regional variation in the epidemiology and management of CKD and that there are challenges in implementing the recommended clinical practice guidelines for patient monitoring, engagement and early delivery, as well as maintenance of effective therapies. To address these issues, this study will create a global cohort that will serve as a platform to improve our understanding of the epidemiology of CKD and its associated comorbidities and complications, as well as the determinants of clinical outcomes and PROs, and will facilitate the long-term goal of improving the management and prognosis of patients with CKD from a range of geographical regions in a real-world clinical setting.

## MATERIALS AND METHODS

DISCOVER CKD is a hybrid, multinational, observational cohort study in patients with CKD comprising a retrospective patient cohort capturing secondary data from established anonymized datasets and a prospective cohort collecting primary and secondary data in patients individually recruited from participating centers in China, Italy, Japan, Sweden, the UK and the USA (ClinicalTrials.gov identifier: NCT04034992). The study aims to be descriptive by collecting data from routine clinical care.

### Study objectives

The study objectives are described in Table 1.

**Table 1. sfab046-T1:** Study objectives

Objective	Description
Primary	To construct a multinational longitudinal cohort of patients with CKD that can be used for the generation of primary and secondary real-world data in order to provide insights into the epidemiology of CKD by describing patient characteristics, disease progression, clinical outcomes, patient journey aspects, practice patterns and clinical management of CKD
Secondary	To develop country-specific descriptions of the primary objectives by different stages of CKD with a focus on the comorbidities and complications of CKD, including hyperkalemia, anemia and diabetes
Exploratory	To evaluate the monitoring and trajectories of laboratory values across different patient subgroups, as well as risk factors (covariates captured at baseline and time varying) associated with CKD progression, e.g. diabetes, and complications of CKD, e.g. hyperkalemia, anemia, diabetes and clinical outcomes

### Patient population and sample size

Adult patients from China, Italy, Japan, Sweden, the UK and the USA with a confirmed diagnosis of CKD from any cause are eligible to participate in the study. CKD will be identified by (i) documented diagnostic code (e.g. International Classification of Diseases 10) for CKD Stages 3A through to kidney failure; (ii) two consecutive eGFR measures of <75 mL/min/1.73 m^2^ [28] recorded >90 days apart (maximum 730 days) from 1 January 2008 (in Japan, eGFR will be calculated using the revised equations for eGFR from serum creatinine in Japan [29]); or (iii) a code for chronic (duration >30 days) renal replacement therapy (hemodialysis and peritoneal dialysis). Patients with a history of kidney transplant are eligible for inclusion. Exclusion criteria include current participation in any interventional trial at baseline (index; prospective cohort only), undergoing treatment for active cancer except for nonmelanoma skin cancer (prospective cohort only), life expectancy of <12 months (prospective cohort only), diagnosis of cancer on or within the 1 year prior to index (retrospective cohort only) and <1 year of medical history available prior to the index date (retrospective cohort only). The study may be supplemented with extended patient follow-up or additional countries and databases/registries.

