There are potential limitations that need to be considered. First, in some instances, patient data included in the retrospective cohort may theoretically be duplicated across databases from the same country. However, that likelihood is small, as a CKD patient at Stage 3A or higher is likely to have a clinical visit at least 2–3 times per year. Therefore the required period of 1-year registration/medical history prior to the index date reduces the likelihood of duplicating patient data. Second, although we aim to collect data systematically and via different methods (as described above), heterogeneity in the coding systems used and the clinical management of patients (e.g. nephrology, general practice, cardiology and endocrinology) might result in differences in the quality of collected data. Nevertheless, because this study will reflect how data are collected in routine practice in the real world, where there are many differences in healthcare settings and treatment choices, these data will provide real-world insights on actual within- and between-country differences, as well as differences between primary and secondary care settings, thereby providing data that are complementary to data collected in randomized clinical trials and can be used to assess the impact these settings have on clinical outcomes. Third, EHR and claims data are not collected for research purposes and may therefore lack information on specific covariates that may be associated with CKD. However, these data will offer important variables, including lab values, as well as provide crucial disease insights and help to contextualize study findings. Missing variables and missing information within variables will be assessed. Fourth, patients may incorrectly recall self-reported information, leading to differential recall bias; for example, incorrect recall of diet or physical activity leading to over-/underestimation of inferences. Finally, the indication for treatment and side effects of therapies may not be recorded. Despite this, treatment indication can be inferred when a product has a single indication and little to no off-label use.

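### The laboratory entry rule admits people with two eGFR values of 60-74 without requiring any kidney-damage marker, while the code rule and the visit-frequency text start at Stage 3A; entry route and this eGFR band should be reported separately.

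*Protocol article*

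**What the plan says.** In the protocol article, Patient population and sample size, the lead-in makes eligible adults "with a confirmed diagnosis of CKD from any cause are eligible to participate in the study". The next sentence says how CKD is identified, through three routes joined by 'or':

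- **Route (i), code:** "documented diagnostic code (e.g. International Classification of Diseases 10) for CKD Stages 3A through to kidney failure".
- **Route (ii), laboratory:** "two consecutive eGFR measures of <75 mL/min/1.73 m^2", "recorded >90 days apart (maximum 730 days) from 1 January 2008". The threshold carries a literature citation. No damage marker is attached.
- **Route (iii), renal replacement:** "a code for chronic (duration >30 days) renal replacement therapy (hemodialysis and peritoneal dialysis").

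Three other places bear on this:

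- The Introduction describes the classification used to diagnose CKD and stratify its risk as resting on "estimated glomerular filtration rate (eGFR) and urinary albumin:creatinine ratio".
- Prospective cohort lists anticipated visit frequencies for Stages 3A, 3B, 4 and 5 only.
- The Discussion plays down duplicate records on the ground that "a CKD patient at Stage 3A or higher is likely to have a clinical visit at least" two to three times a year.

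**The concern.** Routes (i) and (ii) do not describe the same population. By standard staging, Stage 3A begins below an eGFR of 60 (the article does not print the stage cut-offs). A person with values of 72 and 73 four months apart and nothing else on record qualifies by route (ii), but no Stage 3A code would describe that person.

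The primary objective covers patient characteristics, progression, outcomes, practice patterns and management. The case definition sets the denominator for all of these. If a sizeable part of that denominator has mildly reduced eGFR and was never required to show kidney damage, several results can shift:

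- counts of CKD rise;
- progression and event rates can be diluted;
- care can look under-delivered, because some of those counted may not have had an indication for it.

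The study also hypothesises regional variation. If the share entering by route (ii) differs between sources, part of any country difference could come from the entry rule.

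**Working it through.** **1. Entry rules side by side.** No power or sample-size figure is involved, and the plan has no figure of its own to reproduce on this point.

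| Person | Route (i) | Route (ii) | Covered by the Stage 3A text? |
|---|---|---|---|
| Two eGFRs below 60, coded Stage 3A or higher | yes | yes | yes |
| Two eGFRs below 60, not coded | no | yes | yes |
| Two eGFRs of 60-74, no marker, no code | no | **yes** | **no** |

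The third row is the point. The lead-in's reference to a confirmed diagnosis does not remove it, because the next sentence makes that diagnosis operational through the three alternatives.

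**2. How large could the third row be?** The documents give no eGFR distribution, so every input here is an assumption:

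- true eGFR *T* in adults with repeat tests is normal, mean μ from 60 to 90, SD σ of 16 or 20;
- each measured value is *T* plus independent normal error with SD 5.

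With φ(t; μ, σ) the density of *T* and Φ the standard normal distribution function:

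- P(both <75) = ∫ Φ((75−t)/5)² φ(t; μ, σ) dt
- P(both <60) = ∫ Φ((60−t)/5)² φ(t; μ, σ) dt
- P(both 60-74) = ∫ [Φ((75−t)/5) − Φ((60−t)/5)]² φ(t; μ, σ) dt

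The share is P(both 60-74) / P(both <75). The size ratio is P(both <75) / P(both <60). Ratios and shares come from unrounded probabilities.

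| Mean | SD | P(both <75) | P(both <60) | Size ratio | Both 60-74, share of route (ii) | Not both <60, share of route (ii) |
|---|---|---|---|---|---|---|
| 60 | 16 | 0.770 | 0.432 | 1.78 | 26.5% | 43.8% |
| 60 | 20 | 0.725 | 0.445 | 1.63 | 23.6% | 38.6% |
| 70 | 16 | 0.553 | 0.219 | 2.52 | 40.3% | 60.4% |
| 70 | 20 | 0.543 | 0.265 | 2.05 | 33.5% | 51.1% |
| 80 | 16 | 0.318 | 0.084 | 3.81 | 53.6% | 73.7% |
| 80 | 20 | 0.351 | 0.132 | 2.66 | 43.4% | 62.4% |
| 90 | 16 | 0.140 | 0.023 | 5.99 | 64.9% | 83.3% |
| 90 | 20 | 0.191 | 0.054 | 3.55 | 52.6% | 71.8% |

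The share with both values at 60-74 runs from about 24% to 65%, and the size ratio from about 1.6 to 6. The last column is larger because it also counts people with one value on each side of 60: at mean 60, SD 20 they are 38.6 − 23.6 = 15.0% of route (ii), and at mean 90, SD 16 they are 83.3 − 64.9 = 18.4%.

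**3. What the model leaves out.** It covers route (ii) only. Entrants by routes (i) and (iii) are not modelled, so these are not shares of the whole cohort. It has no albuminuria or other damage variable, so it cannot say how many people at 60-74 have CKD.

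**The case against.** The strongest reply is that the threshold is a deliberate choice. It is cited, and the Discussion says that inclusion is meant to be broad across stages rather than limited to advanced disease. The cited source, the full protocol and the master analysis plan are not to hand, and an article may leave a threshold's rationale to them. This stands: the cut-off is not evidently an error. It does not settle the matter, because breadth across stages of CKD still means people with CKD, and the Stage 3A text elsewhere does not fit the rule.

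Second, the secondary objective already plans description by CKD stage, which would tend to separate people at 60-74 from Stages 3A-5. This partly stands. The harm falls mainly on summaries not split by stage, and on the headline count.

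Third, the supporting text is indirect. The Introduction gives background on a classification, the visit frequencies are anticipated, and the Discussion sentence concerns duplicates. None of them defines the population. They are passages to reconcile with the rule, not competing definitions.

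Fourth, making a damage marker a condition of entry would make entry depend on who was tested, which may itself vary by source. And a code for Stage 3A or higher already qualifies by route (i). This stands, and is why the fix keeps the entry rule and works through reporting.

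A reader might also infer that lab-rich and code-based sources must differ in stage mix by construction. The documents do not show that. Every source in Table 2 is EHR or EHR with claims, and none is listed as claims only. Retrospective cohort does allow claims databases, and laboratory coverage may vary, so a difference between sources is a reasonable inference but no more.

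**Conclusion.** The point holds as a should-fix. As written, the laboratory route lets people with two eGFR values of 60-74 into the CKD denominators without any required evidence of kidney damage, and the code route, visit schedule and duplicate-record argument do not cover them. Under the assumed distributions this group is about 24-65% of laboratory-route entrants, and the group below 75 is about 1.6 to 6 times the group below 60. These ranges rest wholly on the assumed means, SDs and normal shape, and on Stage 3A beginning below 60.

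Two stronger readings are not supported. One is that these people do not have CKD: the rule only fails to ask for evidence, and some will have kidney damage. The other takes the larger share that fails two values below 60 (up to 83.3% in the table) as the size of the 60-74 group: that figure includes people with one value below 60. The study is descriptive, so no hypothesis test is invalidated. What is at stake is how counts, rates and country comparisons are read.

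**What to change.** Keep the extraction and the rule of two values below 75, and change what is stated and reported:

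1. State the reason for 75, and reconcile it with the Stage 3A text in Prospective cohort and in the Discussion's limitations.
2. Flag each patient's entry route or routes.
3. Report eGFR 60-74 without a recorded damage marker or CKD code as its own stratum, separate from Stages 3A-5, in counts, outcomes and care-delivery summaries. Say where people with one value on each side of 60 are placed.
4. Give the figure of more than 2 000 000 retrospective patients and the main country comparisons by entry route. As a stated sensitivity analysis, repeat them with laboratory entry restricted to two values below 60.
5. Report by source how many people at 60-74 were tested for a damage marker, since membership of the stratum in item 3 depends on testing.

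The cost is some wording, one flag and extra table columns; no data are lost. The headline cohort is smaller under the stricter definition, and marker status remains only as complete as testing in each source.

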### Prospective cohort

The initial aim is to identify and capture primary and secondary data from a minimum of 1000 (no set maximum) patients with CKD enrolled over a period of 2 years, with prospective follow-up for a minimum of 1 year. Additionally, for patients who agree to participate, patient-specific data will be captured through semistructured qualitative interviews in a randomly selected subset of ∼100 patients (~16–18 patients per country).

Sites have been selected based on an extensive list of physicians, collated with input from the managing contract research organization (PAREXEL), the study sponsor (AstraZeneca) and the DISCOVER CKD scientific committee whose members are listed in the Supplementary data, Table S1.

Eligible patients will be enrolled into the study at the time they routinely visit their physician and consent to participate. The index date will be the baseline visit; the preindex period for each patient is defined as 1 year prior to the index date, where secondary information/data on demographics, clinical assessments, laboratory values, family history, medical history, healthcare resource utilization, procedures and prescription history, as listed in Supplementary data, Table S2, will be extracted from their existing medical records and entered into the electronic case report form (eCRF) after the patient has completed the clinical visit. The number of clinical visits per year based on the current clinical practice recommendations [30] is anticipated to be as follows: CKD Stage 3A, ∼2 times per year; CKD Stage 3B, ∼2 or more times per year; CKD Stage 4, ∼3 or more times per year; and CKD Stage 5, ∼4 or more times per year (guidelines are subject to variation in different countries). This provides opportunities to follow-up with patients and capture data collected during these routine visits [30]. For a patient enrolled prospectively, the potential maximum duration in the study will be ∼3 years, which may be extended. Patients will remain enrolled until study end, study discontinuation/loss to follow-up, withdrawal from the study or death, whichever occurs first.

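### Read literally, the eGFR entry route lets any intervening test break a qualifying pair, so patients without a CKD or dialysis code who are tested more than about four times a year may be missed or enter late

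*Protocol article*

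**What the plan says.** The protocol article ('Patient population and sample size') accepts a patient who meets any one of three criteria joined by 'or':

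- Route (i): "documented diagnostic code (e.g. International Classification of Diseases 10) for CKD Stages 3A through to kidney failure".
- Route (ii): "two consecutive eGFR measures of <75 mL/min/1.73 m^2^ [28] recorded >90 days apart (maximum 730 days", counted from 1 January 2008.
- Route (iii): "or (iii) a code for chronic (duration >30 days) renal replacement therapy (hemodialysis and peritoneal dialysis".

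Only route (ii) has a spacing rule. The article does not say how a test falling between the two qualifying values is treated.

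Three other places bear on the point:

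- Table 1 ('Study objectives') gives as an exploratory aim "To evaluate the monitoring and trajectories of laboratory values across different patient subgroups". The primary objective includes practice patterns and disease progression.
- 'Retrospective cohort' says that this cohort captures incident CKD from 1 January 2008.
- 'Prospective cohort' sets the index date at the baseline visit. It lists the anticipated number of clinical visits by stage, rising from about two a year in Stage 3A, through at least about two in 3B and three in Stage 4, to the last entry: "CKD Stage 5, ∼4 or more times per year".

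**The concern.** The spacing rule is there to show that a low eGFR persists. Tied to consecutive measurements, it works the wrong way round. Take a patient with low values on days 0, 60 and 120. Days 0 and 120 are more than 90 days apart, but they are not adjacent, and neither adjacent pair (60 days each) meets the rule. With the middle test removed, the same patient qualifies. More evidence of persistence makes entry harder.

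Three things are at stake for patients who depend on route (ii):

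- **Selection.** Laboratory-route entry depends on how often a patient is tested, and monitoring is something the study intends to describe.
- **Timing.** In the retrospective incident cohort, where the eGFR pair sets entry, late qualification moves time zero. The one-year history window and the one-year cancer exclusion move with it.
- **Comparability.** The article says that visit guidelines vary by country, and the Discussion concedes heterogeneous coding systems. The effect could therefore differ between countries and databases.

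**Working it through.** The article states no figure on this point, so there is none to reproduce. The check is interval arithmetic followed by simulation.

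**Inputs from the article.** The gap must be more than 90 and at most 730 days, and the two values consecutive and both below 75. **Assumptions.** 'Consecutive' means adjacent in the record; every eGFR is low; the patient has no CKD or dialysis code; the testing rate is constant. The gap patterns are also assumed.

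**Step 1: break-even rate.** With k evenly spaced tests a year the gap is 365.25/k days, and the rule needs a gap above 90. Break-even is 365.25/90 = 4.06 tests a year. Two a year gives 182.6 days, three 121.8 and four 91.3, so all three pass, the last by 1.3 days. Five gives 73.1, six 60.9 and twelve 30.4, and these never pass.

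**Step 2: literal rule against a relaxed rule.** The simulation used 4,000 patients per setting. Gaps were normal with a coefficient of variation (CV) of 10, 20 or 30%, or exponential (irregular). The comparator accepts any test more than 90 and at most 730 days after the first. It is anchored on the first test, so it can only understate the wording proposed as the fix, which allows any pair.

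| Tests/year | Literal rule, qualify within 1 year: CV 10 / 20 / 30% / irregular | Literal rule, within 3 years: same order | Median days, irregular: literal vs comparator |
|---|---|---|---|
| 4 | 97 / 95 / 96 / 85% | 100 / 100 / 100 / 100% | 213 vs 153 |
| 5 | 4 / 42 / 68 / 83% | 14 / 86 / 98 / 100% | 220 vs 140 |
| 6 | 0 / 4 / 27 / 80% | 0 / 13 / 64 / 100% | 226 vs 131 |
| 8 | 0 / 0 / 1 / 68% | 0 / 0 / 1 / 99% | 268 vs 122 |
| 12 | 0 / 0 / 0 / 42% | 0 / 0 / 0 / 87% | 439 vs 111 |

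At 5 to 12 tests a year the comparator admits 98 to 100% within one year. That near-complete figure follows largely from setting every eGFR low.

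**Step 3: sensitivity to regularity and record length.** With n gaps, each exceeding 90 days with probability p, the chance of at least one qualifying gap is 1 − (1 − p)^n.

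- Five a year, two years (10 tests, 9 gaps, mean 73 days). SD 10: p = 1 − Φ(17/10) = 0.0446, giving 1 − 0.9554^9 = 34%. SD 20: p = 1 − Φ(17/20) = 0.198, giving 1 − 0.802^9 = 86%.
- Five a year, ten years (49 gaps), SD 10: 1 − 0.9554^49 = 89%.
- Six a year, two years (11 gaps, mean 60.8 days): 2% with SD 10 and 56% with SD 20. Over ten years (59 gaps) with SD 10: 10%.

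Outright failure therefore needs near-regular testing clearly above the break-even rate. Otherwise the usual result is delay.

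**Step 4: who depends on route (ii).** Routes (i) and (iii) admit coded patients whatever their test spacing. That leaves patients with neither code. They include those with eGFR below 75 who are not yet at Stage 3A, since the codes in route (i) start at Stage 3A.

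**Step 5: effect of the fix.** An adjacent pair has no intervening test, so every pair that meets the literal rule also meets the proposed one. The fix therefore excludes nobody whom the literal rule admits, and nobody qualifies later.

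**The case against.** A reader might infer that the rule shuts out or delays the most advanced patients, because Stage 5 has the highest visit frequency. The article does not support that, for three reasons:

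- Routes (i) and (iii) have no spacing rule and cover coded Stage 3A through to kidney failure and chronic dialysis, which is where advanced patients are most directly provided for.
- The schedule counts anticipated clinical visits in the prospective cohort. Treating it as eGFR testing frequency, or carrying it over to the databases, is an assumption.
- At the stated Stage 5 figure of four a year, an even gap is 91.3 days and passes. Only the 'or more' part could be affected, and Stages 3B and 4 carry the same words.

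Further objections limit the size. Retrospective records may run from 2008 to the latest data, and one gap above 90 days between adjacent low values is enough. A patient observed from early disease, when testing was sparse, may qualify before monitoring becomes frequent, whereas the simulation holds the rate fixed. Rejection percentages depend heavily on the assumed regularity. In the prospective cohort the index is the baseline visit, so a late confirming pair does not move it. All of this stands.

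The last objection is about meaning. 'Consecutive' may be intended as sustained, with no intervening value above the threshold, and the full protocol or the master analysis plan may say so. That reading is possible, but the eligibility sentence does not state it. As printed, the natural reading is adjacency, and that reading gives the worse rule.

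**Conclusion.** The point holds in a limited form. On the ordinary reading of consecutive, regular testing more than about 4.06 times a year prevents qualification by route (ii), and irregular frequent testing mostly delays it. With random timing, the median delay relative to the comparator runs from 220 − 140 = 80 days at five tests a year to 439 − 111 = 328 days at twelve.

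The harm is confined to frequently tested patients without a CKD or dialysis code. They may be lost by this route or, in the retrospective incident cohort, enter late. Coded patients are unaffected as long as the code does not come after the eGFR evidence.

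The net effect on the cohort is unknown. The article gives neither the share of uncoded patients nor any eGFR testing frequency, including for patients not yet at Stage 3A. The simulated percentages describe the rule under assumed gap patterns and are not estimates of loss in this study. The change is still worth making, because the defect is in a stated eligibility rule, it ties entry to something the study describes, and it costs almost nothing to remove.

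**What to change.** In route (ii), replace the requirement for two consecutive measures with: *two eGFR values below the threshold, >90 and ≤730 days apart, with every intervening value also below the threshold*. Apply the same definition in the extraction query for each database. This keeps the protection against a transient low value without penalising frequent testing.

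The cost is one sentence and a small query change. If the query already works this way, only the sentence needs correcting.
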